### 2.9. Ethical Considerations

The protocol is registered in ClinicalTrials.gov ID: NCT05432700. The study will abide by Organic Act 3/2018, of 5 December, referring to personal data protection and the guarantee of digital rights, and by Act 41/2002, of 14 November, regulating patient autonomy and the rights and obligations in relation to information and scientific documentation. Likewise, the ethical principles of the Declaration of Helsinki will be followed. Informed consent will be obtained from all the participating women. LactApp^®^ complies with the policies referring to privacy and cookies, guaranteeing abidance with the measures required by Regulation (EU) 2016/679 of the European Parliament and Council, of 27 April 2016, regarding the protection of physical persons with regard to to personal data and the free circulation of such data, Organic Act 15/1999, of 13 December with regard to data protection (LOPD), and Spanish Royal Decree 1720/2007, of 21 December, with due declaration before the Spanish Data Protection Agency. Likewise, the study will abide by Act 34/2002, of 11 July, on electronic commerce and information regarding the use of cookies (LSSICE), expressly requiring consent from the users registered to the application.

### 2.10. Validity and Reliability

The entire dataset will be confirmed after collection, and any subjects found will be directly amended by the researcher. The identification of obvious errors and outliers in the data will be shown by descriptive analysis. When necessary, data will be double-checked against the original databases.

Factors such as age, education level, employment situation, and previous experience with BF may influence the results of the study. Due to randomization, decompensated key variables between groups are not expected. However, if poorly distributed characteristics are found, these variables will be included as independent variables along with the exposure variables in the multivariate analysis models.

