## Abstract

Purpose: The primary aim of this study is to determine the influence of an intervention in women based on a free mobile application (LactApp^®^, Barcelona, Spain) in maintaining breastfeeding (BF) up to 6 months postpartum. The secondary aim is to assess the effect of health literacy (HL) on breastfeeding duration. Methods: A multicenter, randomized controlled clinical trial of parallel groups will be carried out. Women will be randomly assigned to each of the parallel groups. In the control group, usual clinical practice will be followed from the third trimester of pregnancy to promote BF. In the intervention group, and in addition to usual clinical practice, the women will use a free mobile application (LactApp^®^) from the third trimester to 6 months postpartum. The type of BF at birth, at 15 days and at 3 and 6 months postpartum and the causes of cessation of BF in both groups will be monitored. The hypothesis will be tested using inferential analysis, considering an alpha of 5%. The study protocol was approved by the Clinical Research Ethics Committee of Hospital de la Ribera (Alzira, Valencia, Spain) in February 2021. A per protocol analysis and an intention-to-treat analysis will be performed. Discussion: This study will identify the influence of a mobile application on improving BF rates. If the application proves effective, we will have a tool with free information available to any user at any time of day, which may be complemented by normal clinical practice and be integrated into our health care system. Trial registration: ClinicalTrials.gov ID: NCT05432700.

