### 2.3. Randomization and Blinding

The women will be included during the third trimester of pregnancy in the different primary care midwife consulting rooms of each of the participating centers. After reading the information sheet and giving informed consent, the women will be registered on a webpage created for the purpose of the research and will be assigned to one of the groups (control or intervention) via a simple randomization process, until the estimated sample size has been reached. Randomization will be performed using Epidat v.4.2. [33], with groups of equal size.

Allocation concealment will be carried out, with blinding of the midwives in charge of recruiting the women, providing them with sealed, opaque and sequentially numbered envelopes to be delivered to each new participant wishing the participate in the study.

The research team will prepare the envelopes based on the random allocation sequence. Each envelope will contain a card with a QR code providing access to the study follow-up platform. Follow-up data collection will be conducted by another researcher blinded to the group status of participants. Only the data manager will have access to all of the integrated data (the data reported by the participating women through the surveys and the birth/postpartum data reported by the principal investigators).

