### 2.7. Baseline Variables

The following variables will be collected at baseline:

- Sociodemographic variables: maternal age at the probable date of delivery, country of origin (Spain/foreign), level of education (primary school or lower/secondary school/university), employment status (self-employment/professional/managerial employment/employee/unemployed/student/not looking for a job), civil status (single/married/separated-divorced), partner (yes/no), number of live offspring, previous experience with breastfeeding (yes/no), participation in maternal education groups (yes/no), reception of previous information on BF (yes/no), and participation in BF support groups (yes/no).

- Variables related to health literacy: as a screening tool, use will be made of the HLS-EU-Q16, which evaluates the HL of the population based on 16 items scored by means of a Likert scale from “very easy” to “very difficult”. This is a unifactorial scale with good internal consistency as measured by McDonald’s omega, with a value of 0.982 in the Spanish population [34].

- Variables referred to health-related quality of life: use will be made of the EQ-5D [40] in the baseline measurements and at 3 and 6 months. This scale is very sensitive to quality of life measures and has been shown to be even more sensitive in women [41]. It comprises 5 items related to mobility, personal care, daily activities, pain/discomfort, and anxiety/depression. It uses a visual analogue scale (VAS) from 0 to 100 for measuring health condition at the time of application of the questionnaire [42].

- Variables related to self-efficacy of BF: the measurement of self-efficacy will be made with the BSES-SF scale in its Spanish version [37]. This instrument consists of 14 items scored by means of a Likert scale from 1 (not at all) to 5 (always). The BSES-SF is a unidimensional scale with a Cronbach alpha of 0.79 in its Spanish version.

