- Obstetric-neonatal variables. The following information will be collected retrospectively from the electronic case history: gestational age (days) at the time of birth, parity (none/one or more), type of previous deliveries (none/eutocic/other), onset of labor (spontaneous/induced/stimulated), rupture (spontaneous/artificial), group B streptococcus (positive/negative), intrapartum antibiotic use (yes/no), intrapartum analgesia (inhalatory/local/epidural/none), Kristeller maneuver (yes/no), completion of delivery (eutocic vaginal/eutocic instrumental (vacuum, spatulas, forceps), intrapartum cesarean section), episiotomy (yes/no), perineal condition following birth (intact/grade 1/grade 2/grade 3/grade 4), newborn gender (female/male), newborn weight (grams), Apgar score, umbilical arterial pH at birth, early skin-to-skin contact (within 30 min and lasting for at least 2 continuous hours) (yes/no/with father), early start of breastfeeding (within 2 h/after more than 2 h), drinking allowed during delivery (yes/no), accompaniment of maternal choice allowed (yes/no), mobilization allowed during delivery (yes/no), and positioning in moment of birth (vertical/lying down—lithotomy position/lateral decubitus).

- Response variable: type of nursing (BF/SF/MF) at 6 months postpartum, to assess newborn and infant feeding practices, with the following options: (a) BF, including extracted or donor milk. The infant only receives drops or syrups (vitamins, mineral, medicines); (b) SF (supplementary feeding), where infant feeding is limited to artificial formulas and solid; and (c) MF (mixed feeding), where infant feeding combines BF and SF. All women intend to offer BF after birth. The response variable “Suspension of BF at 6 months” (yes/no) will be considered, where “yes” means the infant is receiving SF and “no” means the infant continues with BF or MF at 6 months.

- Variables related to suspension of BF: type of suspension (total or partial), cause of early suspension (before 6 months postpartum), and total duration of BF in full days from time of birth.

- Follow-up variables: participation in support groups, and number of midwife/pediatrician/pediatric nurse visits during the first 6 months. Even if women suspend BF, the number of visits to these health professionals will continue to be counted for up to 6 months.

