### 2.8. Data Analysis

An analysis will be performed of the baseline characteristics between the group of possible losses to follow-up and the group of women that complete follow-up, based on two-input tables and the comparison of means, using the Fisher exact test or Mann–Whitney U-test, as applicable.

Testing of the homogeneity of groups will be completed regarding the baseline variables and birth-related parameters and the suspension of BF at 6 months, using two-input tables and the chi-square test (χ^2^) or Fisher exact test, as applicable, while the comparison of means will be performed using the Mann–Whitney U-test.

A per-protocol (PP) analysis and intention-to-treat (ITT) analysis will be carried out. In the PP analysis, continuous variables will be reported as the mean and standard deviation (SD), or as the median and interquartile range (IQR) in the case of a non-normal data distribution, while categorical variables will be reported as frequencies and percentages. Data normality will be assessed using the Kolmogorov–Smirnov test.

In the ITT analysis, sensitivity referring to losses during follow-up will be assessed, with the response variable of the intervention group being assigned the worst result possible (suspension of BF at 6 months) and the control group being assigned the best result possible (no suspension of BF). Evaluation of the differences in response variable between the two groups will be performed, with all randomized subjects, applying the chi-square test.

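### The imbalance rule for choosing covariates does not exclude variables that arise after randomization, so the adjusted odds ratio may lose part of the app's effect

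*Protocol article*

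**What the plan says.** - **Rule (2.10).** Age, education level, employment and previous breastfeeding experience are given as examples of factors that may influence the results. Randomization is expected to balance them. Then: "if poorly distributed characteristics are found, these variables will be included as independent variables along with the exposure variables in the multivariate analysis models". There is no threshold and no closed list.
- **Screen (2.8).** "Testing of the homogeneity of groups will be completed regarding the baseline variables and birth-related parameters", by chi-square or Fisher tests and by Mann–Whitney tests. The other covariate comparison in 2.8 sets women lost to follow-up against completers, so this is the only check between arms.
- **Variable list (2.7).** It opens with "The following variables will be collected at baseline". Below that stand self-efficacy ("the measurement of self-efficacy will be made with the BSES-SF scale in its Spanish version") and the obstetric-neonatal items, among them "early skin-to-skin contact (within 30 min and lasting for at least 2 continuous hours" and "early start of breastfeeding (within 2 h/after more than 2 h".
- **Timing.** Section 2.3: "The women will be included during the third trimester of pregnancy". The Abstract has the intervention group using the app "from the third trimester to 6 months postpartum". Section 2.5.1 mentions the BSES-SF only with the e-mails sent after birth.
- **Where the rule acts (2.8.1).** Suspension of breastfeeding at 6 months is compared by chi-square test and also by multivariate logistic regression with an odds ratio. No covariates are named.

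**The concern.** A covariate in a treatment-effect model should be fixed before the treatment can act on it. A variable measured later may lie on the path from treatment to outcome. Conditioning on it then estimates only the part of the effect that does not pass through it, and that is not the question this trial asks.

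An imbalance rule makes this worse, because it reacts to differences between arms. For a true baseline variable a difference is chance. For a variable the app can change, a difference may be the app working. The more the app moves early start or self-efficacy, the more likely that variable is to be flagged and adjusted for. What is at stake is the meaning of the adjusted odds ratio for the primary outcome, whose model also stays unknown until the arms have been compared.

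**Working it through.** The protocol gives no figure of its own on this point. Its 60% and 40% suspension rates, 399 women, 20% losses and 87.7% early start (Introduction, a selected local sample) serve as inputs. Everything marked assumed is mine.

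**1. What the screen can reach.** Section 2.7 lists 11 sociodemographic variables, health literacy, EQ-5D, BSES-SF and 22 obstetric-neonatal items: 11 + 3 + 22 = 36. Of the 22, parity and type of previous deliveries precede randomization, which leaves about 20 recorded around or after birth. Most of these are not plausible consequences of the app (newborn sex cannot be). Skin-to-skin contact and early start could be. So could the BSES-SF: the Discussion cites a meta-analysis of 15 randomized trials in which mobile health interventions improved breastfeeding self-efficacy.

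**2. Chance flags if the app changes nothing.** P(at least one) = 1 − (1 − α)^k, with independent tests (assumed).

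| k | α = 0.05 | α = 0.005 |
|---|---|---|
| 36 listed variables | 1 − 0.95^36 = 84% | 1 − 0.995^36 = 17% |
| 20 birth variables | 1 − 0.95^20 = 64% | 1 − 0.995^20 = 10% |

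Both levels appear in the article (5% in the Abstract and 2.4; 0.005 in 2.8.2), and 2.10 ties its rule to neither.

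**3. Chance that a variable moved by the app is flagged.** 399 × 0.8 = 319, about 160 per arm. Power of a two-sided two-proportion test, with early start at 87.7% in controls:
- 93% with the app (assumed): flagged in 36% of trials at 0.05, 11% at 0.005.
- 97% with the app (assumed): flagged in 88% at 0.05, 63% at 0.005.

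**4. What adjustment then does.** The planned total odds ratio is (0.40/0.60) / (0.60/0.40) = 0.444. Let early start have prevalence p0 in controls and p1 with the app, and odds ratio θ on suspension (all assumed except p0 = 87.7%). Solve for the intercept a and the direct effect d:
- p0·expit(a + ln θ) + (1 − p0)·expit(a) = 0.60
- p1·expit(a + d + ln θ) + (1 − p1)·expit(a + d) = 0.40

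The adjusted odds ratio is exp(d). The share of the log odds ratio removed is 1 − d/ln(0.444).

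Worked case (p0 = 87.7%, p1 = 97%, θ = 0.33). Control suspension is 57.2% with early start and 80.2% without: 0.877 × 0.572 + 0.123 × 0.802 = 0.60. With the app it is 39.2% and 66.1%: 0.97 × 0.392 + 0.03 × 0.661 = 0.40. Adjusted odds ratio: (0.392/0.608) / (0.572/0.428) = 0.48.

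| p0 | p1 | θ | adjusted OR | share removed |
|---|---|---|---|---|
| 87.7% | 93% | 0.50 | 0.457 | 3.5% |
| 87.7% | 93% | 0.33 | 0.461 | 4.6% |
| 87.7% | 97% | 0.50 | 0.470 | 7.0% |
| 87.7% | 97% | 0.33 | 0.483 | 10.2% |
| 70% | 93% | 0.50 | 0.514 | 18.0% |
| 70% | 93% | 0.33 | 0.554 | 27.1% |
| 70% | 97% | 0.50 | 0.529 | 21.5% |
| 70% | 97% | 0.33 | 0.579 | 32.7% |

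The calculation assumes no common cause of early start and suspension.

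**5. Selection by imbalance alone.** Simulation under no treatment effect: 1,500 trials of 320 women, 30 independent pre-randomization covariates, 5 of them prognostic, flagged at |z| > 1.96. Type I error at 5% was 4.7% unadjusted, 4.3% with flagged covariates, 5.3% with the 5 prognostic covariates fixed, and 5.7% if the better of unadjusted and flagged is reported. The Monte Carlo standard error is √(0.05 × 0.95/1500) = 0.6 percentage points, so no harm of note shows.

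**The case against.** The best defence is that section 2.10 defines no pool. Every factor it names precedes randomization, and its reasoning, that randomization should prevent imbalance, fits only such variables. Section 2.8 names birth-related parameters separately from baseline variables, and its sentence goes on to suspension at 6 months, so it does more than screen covariates. The heading of 2.7 is loose: the same list holds the 6-month outcome and app use, which nobody would adjust for as baseline.

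This stands in part. A reader might infer that the protocol commits to adjusting for birth events. It does not say so; that comes from joining three sections. But the one between-arm check includes birth-related parameters, 2.10 speaks of characteristics without limit, and nothing excludes the later ones. An analyst who follows the text could include them in good faith.

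Other stronger readings are not supported:
- **That the whole primary analysis is biased.** The chi-square test and the worst-case intention-to-treat comparison carry no covariates.
- **That chance imbalance is near certain.** The 84% needs independent tests at 5%. Several items are linked (group B streptococcus and antibiotics, episiotomy and perineal condition), and at 0.005 the figure is 17%.
- **That hospital or strong predictors are left out, at a quantifiable loss of precision.** The article names no covariates, does not say that only imbalanced ones enter, and gives no data on prognostic strength. A fuller plan may settle this.

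**Conclusion.** The point holds for the adjusted odds ratio in 2.8.1 and for nothing beyond it. This is a rule stated in the protocol and badly fixed, not a detail left to the analysis plan. It lets observed differences choose the model and does not bar variables that arise under exposure to the app.

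The size cannot be determined from the document. If early start is already near 88%, adjusting for it removes about 3.5% to 10% of the planned log odds ratio in the scenarios tried. If it is 70% in controls and the app raises it strongly, 18% to 33%. These rest on assumed prevalences and associations. I have not quantified self-efficacy, for which the article's own citation makes an app effect most plausible. The harm comes from adjusting for post-randomization variables; selection by imbalance in itself does little to type I error. The matter should be corrected, but it does not threaten the unadjusted comparison.

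**What to change.** Replace the rule in 2.10 with a covariate set fixed before the arms are compared and limited to pre-randomization variables. The four factors named there (age, education, employment, previous breastfeeding experience) would serve, included whatever the observed balance. State that variables arising after randomization do not enter the treatment-effect model: labour and birth events, skin-to-skin contact, early start, BSES-SF measured after birth, and visits. Report them descriptively by arm or in a separate mediation analysis. In 2.7, separate true baseline variables from later ones, and say when the BSES-SF is first measured. Keep the comparison of arms in 2.8 as description, not as a selection device.

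The cost is wording, since the four covariates are already collected. There are two trade-offs. The adjusted odds ratio is conditional on the chosen covariates and need not equal the unadjusted one even under perfect balance. A chance imbalance in another baseline variable is then handled only in a sensitivity analysis.

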## 3. Discussion

The purpose of this trial is to explore the impact of an intervention program based on the use of a mobile application in maintaining breastfeeding up to 6 months postpartum. The null hypothesis is that the LactApp^®^ mobile application does not improve the maintenance of BF at 6 months postpartum versus usual clinical practice.

Breastfeeding is not only a physiological process but also entails cultural learning, causing mothers to actively seek information [19]. Nowadays, online communication options have been incorporated into this active search for information [24], and the adoption of such new technologies has been associated with improved nursing rates [43,44]. Although not under professional influence, the use of information and communication technologies in daily life must be acknowledged, and such tools should be used as a means to disseminate quality information based on evidence [45]. In 2018, 67.3% of the Spanish population used the Internet to obtain information on health, and in this regard, mobile applications constitute a growing contribution in the field of information and communication technology [45]. Health professionals must make efforts to consolidate their position as a reference in these new settings as well. If they prove effective and acceptable to the population for which they are intended, instruments of this kind could be introduced as intervention tools for promoting and maintaining BF.

An important percentage of users increasingly take an active role in issues related to health and illness and their relation to the sociosanitary system [46], leaving behind the passive or mere spectator roles of the past [47]. In this context, it is a fact that pregnant women comment to their midwife what they have read on the Internet, and wish to discuss such information [45]. At present, three out of every four users consult the Internet with regard to health issues. This process of empowerment defines the “expert patient”, who seeks information both before and after visiting a healthcare professional [48]. Thus, it must be accepted that in contemporary maternity care, women routinely and massively use online sources to obtain information about their pregnancy, and consequently the maternal–infant health services should adopt strategies that take this phenomenon into account [49]. Such consideration also applies to breastfeeding, where the tendencies are changing, and women now seek online information about infant feeding just as often as they tend to consult nearby family and friends [50], receiving both online support and information through social networks, video calls, or mobile applications [51]. A recent systematic review and meta-analysis [15] of 15 randomized controlled trials (RCTs) of mHealth interventions for BF found that these interventions significantly increased EBF rates at 1, 2, 3, and 6 months postpartum and improved BF self-efficacy, but not attitudes. Updated applications are needed in the latest recommendations on nursing [49,52], with external evaluation guarantees.

Thus, the traditional care model must integrate electronic devices and information and communication technologies to ensure improved performance, since reliance upon healthcare professionals could decrease, giving way to the availability of interactive information through the different technological platforms [15,53]. Health-related applications, mobile phones, blogs, and specific websites are typically used by women of childbearing age and may help improve the experience of pregnancy and motherhood. It is essential for both professionals and health supervisors to be aware of these new developments, which can influence the health of women, and to anticipate the imminent change in care model [54,55].

